#### Planned statistics

The primary analysis will be for the intention-to-treat (ITT) population including all patients randomized and having had the liver transplantation performed. A per-protocol analysis with all patients without major protocol violations will also be performed.

Demographic and clinical parameters will be displayed with mean and standard deviation and median, minimum and maximum for continuous variables. Categorical variables will be shown via absolute and relative frequency. Furthermore, differences between the groups are calculated using Student’s *T* test or the Mann Whitney *U* test and the chi-squared test. The primary endpoint, time to incisional hernia over a period of 12 months, will be compared using a log-rank test. Additionally, we will also be plotting Kaplan-Meier survival curves by group looking at time to hernia development.

For sensitivity analysis a Cox regression analysis adjusted for age and MELD score will further be performed. Subgroup analyses for immunosuppression therapy (everolimus)-specific differences are planned. A *p* value < 0.05 will be statistically significant. We perform our analyses with SPSS v25.0 (SPSS Inc., Chicago, IL, USA).

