### Endpoint

#### Primary endpoint

The primary endpoint of the study is the comparison of the time to incisional hernia over a period of 12 months between the two groups of patients with and without prophylactic mesh placement. Definition of incisional hernia: any detectable defect in the abdominal wall with intra-abdominal contents protruding beyond the aponeurosis [21].

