#### Data management and statistical analysis

Almost all patients after liver transplantation will receive their post-transplant follow-up in our center; therefore, patients will come for a routine check-up and at the same time this is the follow-up for the study. The data for patients will be collected until 24 months after liver transplantation or until they drop out (revision surgery, death, withdrawal, loss to follow-up). We will use a data monitoring committee (DMC).

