#### Sample size estimation

We estimate from the current data that about 20% of patients will develop an incisional hernia in the standard group 1 year after surgery. In the intervention group in which we use Phasix™ (Bard – Davol Inc., Warwick, RI, USA) the prevalence of incisional hernia should drop to 5%.

Considering these assumptions and a level of significance of 5% and a power of 80%, we need to include 81 patients per group using a log-rank test. With regard to a drop-out rate of 10%, 178 patients need be included in the study.

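### Deaths are classed as drop-out and hernia incidence is to be shown by Kaplan-Meier, which modestly overstates the proportion of recipients who develop a hernia

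*Protocol article*

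**What the plan says.** All references are to the protocol article.

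- **Primary endpoint:** "comparison of the time to incisional hernia over a period of 12 months between the two groups of patients", with and without mesh. The Secondary endpoint section repeats this over 24 months.
- **Data management and statistical analysis:** data are collected to 24 months "or until they drop out (revision surgery, death, withdrawal, loss to follow-up"). Death sits in one list with reasons after which a hernia can still occur.
- **Planned statistics:** "The primary endpoint, time to incisional hernia over a period of 12 months, will be compared using a log-rank test". The curves come in addition: "we will also be plotting Kaplan-Meier survival curves by group looking at time to hernia development". A model follows: "For sensitivity analysis a Cox regression analysis adjusted for age and MELD score will further be performed". No competing-risk method is named.
- **Sample size estimation:** the design contrast is stated in proportions of patients: "about 20% of patients will develop an incisional hernia in the standard group 1 year after surgery", while with the mesh "the prevalence of incisional hernia should drop to 5" percent. The Discussion section repeats the 20% to 5% hypothesis.

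**The concern.** A patient who withdraws or is lost may still develop a hernia unseen. A patient who dies cannot. Kaplan-Meier treats every censored patient as still able to have the event, so with deaths censored it estimates incidence in a hypothetical setting without death. The aim of the study and the sample size are stated in a different quantity: the share of liver recipients who get a hernia within a year. Death is foreseeable in patients transplanted for end-stage liver disease, and the article itself lists it.

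At stake are the incidences read off the curves at 12 and 24 months. They would be too high in both arms. Equal mortality does not cancel the error in the absolute difference, because the overstatement is larger where hernias are more frequent, that is, in the control arm if the mesh works. The error therefore flatters the mesh slightly.

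**Working it through.** **Inputs.** From Sample size estimation: 12-month hernia proportions 20% (control) and 5% (mesh), significance level 5%, power 80%, 81 per group, drop-out 10%, total 178. From Data management and statistical analysis: death is one of four drop-out reasons. Mortality is not given and is assumed below.

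**1. The plan's own figure.** The hazard ratio is ln(0.95)/ln(0.80) = 0.2299. Freedman's log-rank formula, taken two-sided, gives (1.960 + 0.842)² × [(1 + 0.2299)/(1 − 0.2299)]² = 20.02 events. The mean event probability is (0.20 + 0.05)/2 = 0.125, so 20.02/0.125/2 = 80.07, or 81 per group. Drop-out: 162 × 1.10 = 178.2, that is 178. The stated figures reproduce.

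**2. Formulas.** With constant hazards, λh for hernia and λd for death:

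- One minus Kaplan-Meier, deaths censored: 1 − exp(−λh·t).
- Cumulative incidence, death competing: λh/(λh + λd) × [1 − exp(−(λh + λd)·t)].

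For hernia, λh = −ln(0.80) = 0.2231 in the control arm and −ln(0.95) = 0.0513 in the mesh arm. For death, λd = −ln(1 − 12-month mortality), equal in both arms.

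**3. Example at 12 months, 10% mortality.** λd = 0.1054.

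- Control: 0.2231/0.3285 × (1 − 0.80 × 0.90) = 0.6793 × 0.28 = 19.02%.
- Mesh: 0.0513/0.1567 × (1 − 0.95 × 0.90) = 0.3274 × 0.145 = 4.75%.
- Difference: 14.27 points, against 15.00 by Kaplan-Meier.

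**4. Range at 12 months** (Kaplan-Meier 20.0% and 5.0%, difference 15.0).

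| Assumed mortality | Control | Mesh | Difference | Overstatement of difference |
|---|---|---|---|---|
| 5% | 19.51% | 4.88% | 14.6 | 0.4 |
| 10% | 19.02% | 4.75% | 14.3 | 0.7 |
| 15% | 18.52% | 4.62% | 13.9 | 1.1 |
| 20% | 18.00% | 4.49% | 13.5 | 1.5 |

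The ratio of the two incidences stays at about 4.0 throughout. A simulation with 400,000 patients per arm agreed with these values to within about 0.1 points.

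**5. Timing of deaths.** If all deaths came before any hernia, the cumulative incidence would be the Kaplan-Meier value times (1 − mortality). At 10% mortality that is 18.0% and 4.5%, a difference of 13.5 and an overstatement of 1.5 points. At 20% it is 16.0% and 4.0%, an overstatement of 3 points.

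**6. At 24 months**, carrying both hazards forward unchanged (a further assumption), Kaplan-Meier gives 1 − 0.80² = 36.0% and 1 − 0.95² = 9.75%, a difference of 26.25 points. The same formula with t = 2 gives:

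- 5% deaths per year: 34.3% and 9.3%, difference 25.1, overstated by 1.2 points.
- 10% deaths per year: 32.7% and 8.8%, difference 23.9, overstated by 2.3 points.

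**The case against.** **The effect at the primary time point is small.** Drop-out as the article defines it includes death, and the allowance is 10% in total. If that allowance covers the first 12 months (its period is not stated), deaths alone should not exceed 10%, and the difference shifts by at most 0.7 points under constant hazards. With 81 per arm, the standard error of the difference is √(0.20 × 0.80/81 + 0.05 × 0.95/81) = 5.1 points, so a 95% interval is about ±10 points. This stands, and it is why the point is one of modest size.

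**The handling of death is inferred.** The drop-out list says when data collection ends, which at death it must, and no censoring rule is written out. That is fair. Yet the methods named for time to hernia are log-rank, Kaplan-Meier and Cox, and in each of them a patient whose record ends without a hernia is censored unless another rule is given. The article gives none.

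**The primary test is unaffected.** This stands: with deaths censored, the log-rank test compares cause-specific hazards and is valid for that.

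**A stronger reading that the article does not support.** A reader might infer that the trial will produce no estimate of the 20% against 5% contrast, that the Cox hazard ratio is the only planned estimate, or that no confidence interval will be reported. The Kaplan-Meier curves do give 12-month proportions by arm. On intervals the article is silent, and a condensed article commonly leaves the effect measure and its interval to an analysis plan. Nor does the article suggest that mortality will differ between arms; the figures above assume that it does not.

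**Conclusion.** The point holds as a cheap improvement of modest size. The direction is certain wherever deaths before hernia occur and are censored: one minus Kaplan-Meier exceeds the proportion of recipients who develop a hernia. At 12 months, with 5% to 10% mortality, the overstatement is about 0.5 to 1.0 points in the control arm, 0.1 to 0.25 points in the mesh arm and 0.4 to 0.7 points in the difference. These sizes rest on an assumed mortality, equal in both arms, and on constant hazards. They grow with higher or earlier mortality and at 24 months, which is a stated secondary endpoint. The relative effect hardly moves. Neither the log-rank test nor the sample size of 81 per group needs to change.

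**What to change.** - Keep the log-rank test as the primary comparison, and describe it as a test of the cause-specific hernia hazard with deaths censored.
- Replace or supplement the Kaplan-Meier curves with Aalen-Johansen cumulative incidence curves by arm, with death before hernia as a competing event.
- From these curves, report the 12-month and 24-month risk differences between arms with 95% confidence intervals.
- Report the number of deaths by arm, separately from withdrawal and loss to follow-up.

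Cost: a change of wording and a short extra analysis, possibly outside SPSS v25.0 if that version lacks the estimator. No further patients or visits are needed, provided that dates of death are recorded, as follow-up ending at death implies. The reported incidences will be slightly lower than the Kaplan-Meier values.

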#### Sample size estimation

We estimate from the current data that about 20% of patients will develop an incisional hernia in the standard group 1 year after surgery. In the intervention group in which we use Phasix™ (Bard – Davol Inc., Warwick, RI, USA) the prevalence of incisional hernia should drop to 5%.

Considering these assumptions and a level of significance of 5% and a power of 80%, we need to include 81 patients per group using a log-rank test. With regard to a drop-out rate of 10%, 178 patients need be included in the study.

#### Privacy

All included patients are coded with continuous numbers (pseudonymization). The data to be evaluated are saved at the Department of Surgery, Division of General Surgery and Division of Transplantation Surgery and only labeled with this number, using an Excel sheet data base on a computer with access restriction, and then assessed. Only authorized persons have access to the original data. Data will be stored for 15 years. Plans for investigators and the sponsor to communicate trial results to participants and healthcare professionals include publications and participation at scientific meetings.

#### Quality assurance

The principles of the International Conference on Harmonization-Good Clinical Practice (ICH-GCP) guidelines [23], the regulations of the Declaration of Helsinki [24] and local legal and regulatory requirements will be adhered to at all times during the trial period. Important protocol modifications will be managed according to the appropriate guidelines. Ancillary care or compensation to those who suffer harm from trial participation is covered by study-related insurance.

## Discussion

Due to a high incidence of incisional hernia after liver transplantation, patients would profit to a great extent from hernia prevention. Borab et al. [14] showed the benefits of prophylactic mesh placement in elective midline laparotomy, lowering the risk for the need for a second operation due to reducing the incidence of developing an incisional hernia. From our perspective there is a high variance for the incidence of developing an incisional hernia after liver transplantation. This variance is due to the different types of incisions used for liver transplant surgery. The transverse incision with subcostal extension has a high risk for developing an incisional hernia. J-shaped incisions seem to be associated with a lower risk but are still unsatisfactory. Placing a long-term resorbable mesh in an onlay position might improve the stability of the tissue and reduce the forces on the scar during the healing process until the mechanical strength of the resorbable mesh is resolved after 12 months and the scar tissue is stable. From our point view we hypothesize that this technique will reduce the incidence of developing incisional hernia from an estimated 20% to 5%.

For placement of the mesh the fascia needs to be dissected from the fatty tissue; this surgical step is associated with a minimally elevated risk for developing seroma, while the risk for surgical-site infection is reduced by the precise wound-closure technique and the choice of mesh material. The risk for the included patients is very low. The potential risks are wound-healing disorder, seroma, hematoma and mesh infection; all of which are evenly associated with the standard procedure.

### Trial status

Recruitment started on 1 January 2018. The protocol version of the study protocol is 3.0 from 18 April 2017; the protocol version of this manuscript is 1.4, 7 October 2018. Recruitment will be approximately completed in December 2021.

## Data Availability

There is no data available yet; patient enrollment started in January 2018.
